**14. SAMPLE SIZE**

Standard care for diabetes using metformin has been reported to reduce HbA1c by 1% and the intervention adds an extra 0.5% (Amod et al., 2012; Pal et al., 2013:22). Assuming a standard deviation of 1 and an alpha error level of 5%, the two-tailed calculation gives a power of over 90% with only 90 participants in each of the control and intervention group. If 20% loss of participants to follow-up is considered (Islam et al., 2014), a total of 108 participants is required in each group.

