**15. RANDOMISATION AND BLINDING**

In order to avoid sharing of messages among diabetic patients, different districts will be used for the control and the intervention. The guideline for the management of diabetes is similar across all the primary health centres in South Africa (Amod et al., 2012), thus, all the primary health care centres are eligible. Of all the eight municipalities/districts, two were conveniently selected. In each selected district, the diabetes clinics were assessed for available facilities such as human resources, HbA1c testing, available diabetes support programmes. The information were obtained from the various facilities or unit heads as deemed appropriate. The obtained information were scored and used to stratify the diabetes clinics into two levels; average and low resourced clinics. All the clinics were assigned an identification number which were hidden from the study statistician. One average-resourced and two low-resourced clinics were selected from the two selected districts, summing up to 6 clinics; 4 low resourced and 2 high resourced clinics. From the clinics selected, demographic and other basic information were obtained to screen for eligibility. From the sample size calculation, 108 participants are required in both arms of the study, therefore, 36 participants are required from each of the six selected clinics. After the collection of the baseline data, randomisation will take place, where individuals are randomly assigned to either the intervention or the control arm using a simple randomisation technique with a 1:1 allocation ratio using the assigned ID numbers. The study statistician will randomly select 36 participants from the list of eligible participants from each clinic, adjusting for age and mean duration of diabetes. Participants in the intervention arm will then be contacted to ascertain their preferences in terms of the preferred language of communication; either the locally spoken Xhosa language or English, preferred time of receiving SMSs, name and contact of next of kin or the available support person.

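### Minor arithmetic error: Section 14 allows for 20% loss by multiplying 90 by 1.2, so 108 per group leaves about 86 evaluable rather than 90; power of over 90% still holds, with almost no reserve

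*Protocol*

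**What the plan says.** Protocol Section 14 (Sample size) takes an added HbA1c reduction of 0.5 from the intervention, a standard deviation of 1 and a two-tailed 5% test, and states "a power of over 90% with only 90 participants in each of the control and intervention group". It then allows for 20% loss to follow-up and states that "a total of 108 participants is required in each group".

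Section 15 (Randomisation and blinding) carries the number forward: "108 participants are required in both arms of the study, therefore, 36 participants are required from each of the six selected clinics". Six clinics of 36 make 216, which is 2 × 108, so Section 15 also treats 108 as a per-arm figure.

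**The concern.** Section 14 puts three numbers together: 90 per group for the stated power, 20% loss, and 108 per group enrolled. They cannot all hold. If 108 are enrolled and 20% are lost, fewer than 90 remain. The usual slip that gives this pattern is to add 20% to the evaluable number instead of dividing it by the fraction retained.

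The evaluable number matters here because Section 21 analyses observed data from all randomised participants and names no method for filling in missing outcomes. Power therefore follows the number actually measured at six months. A reader of Section 14 would expect 180 measured participants, whereas the protocol's own loss rate gives 172. The sample-size paragraph is also likely to be reused in the thesis and papers planned in Section 23.

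**Working it through.** **Inputs, all from Section 14 unless noted**

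- Difference δ = 0.5, standard deviation σ = 1, two-sided α = 5%
- Evaluable per group: 90
- Loss to follow-up: 20%
- Enrolled per group: 108
- Allocation 1:1 (Section 15)

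**Step 1: reproduce the stated power with 90 per group.** Normal approximation: power = Φ(δ / (σ√(2/n)) − 1.96).

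- n = 90: 0.5 × √45 = 3.354; 3.354 − 1.960 = 1.394; Φ = 91.8%
- Two-sample t-test (non-central t), n = 90: 91.6%

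The claim of over 90% with 90 per group is reproduced by either method.

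**Step 2: reproduce 108.**

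- 90 × (1 + 0.20) = 108, exactly the stated figure
- 90 / (1 − 0.20) = 112.5, rounded up to 113, which is 5 more per group

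**Step 3: what 108 delivers.**

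- At 20% loss: 108 × 0.8 = 86.4, so about 86 per group and 172 in total
- Loss at which 90 remain: 1 − 90/108 = 16.7%

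**Step 4: power at and around 86 per group.** Losses are out of 108.

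| Evaluable per group | Lost (share of 108) | Power, t-test | Power, normal approx. |
| --- | --- | --- | --- |
| 90 | 18 (16.7%) | 91.6% | 91.8% |
| 86 | 22 (20.4%) | 90.3% | 90.6% |
| 85 | 23 (21.3%) | 89.99% | 90.3% |
| 84 | 24 (22.2%) | 89.6% | 89.98% |

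The smallest n that reaches 90% power is 86 by t-test and 85 by normal approximation. The 90% mark is therefore missed from 21.3% loss (t-test) or 22.2% loss (normal approximation). Section 14 does not say which formula was used.

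**Step 5: is 108 enough for 90% power at 20% loss?** 86/0.8 = 107.5, so 108. It is enough, with nothing to spare.

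**The case against.** The best defence is that 108 happens to be the right recruitment number for 90% power with 20% loss, as Step 5 shows. Section 14 claims only power of over 90%, not 91.6%, and 90 per group was already a little above the minimum. This stands, and it limits the consequence: the design number supports the stated power at the stated loss.

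It does not rescue the text. Section 14 names 90, not 86, and applies the allowance to 90. One could also read the 20% as a share of the 90 completers, which makes 18 lost and 108 enrolled. Loss to follow-up is ordinarily counted against those enrolled, and Section 14 gives no other definition.

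A reader might draw three stronger conclusions, none of which the protocol supports:

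- *The trial is underpowered because of this slip.* On the protocol's inputs, 86 per group still gives 90.3% to 90.6%.
- *Any loss above 20% takes power below 90%.* Having 86 of 108 evaluable is already 20.4% loss, with power above 90%. At 21.3% loss the t-test figure is 89.99%, a miss of 0.01 of a percentage point, and the normal approximation is still 90.3%.
- *The 36-per-clinic target in Section 15 is wrong.* It follows from 108, and 108 is adequate for the power claimed.

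**Conclusion.** The allowance is wrong as written, and nothing elsewhere in the protocol corrects it. At 20% loss, 108 per group leaves about 86 evaluable, 4 fewer per group and 8 fewer in total than Section 14 implies. Power falls by about 1.2 to 1.3 percentage points, and the claim of over 90% survives. What is lost is the reserve, which runs out at about 21–22% loss.

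This is a minor correction. It takes the difference of 0.5 and the SD of 1 at face value and assumes that loss is counted against those enrolled. Those inputs are for HbA1c, whereas Section 17.1 makes random blood glucose the primary outcome. Whether the power figures carry over is a separate point and does not affect the arithmetic here.

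**What to change.** Restate the last sentence of Section 14, for example: *108 per group leaves about 86 evaluable after 20% loss (about 90% power for a difference of 0.5 SD), or 90 evaluable after 16.7% loss.*

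Nothing else has to change. Section 15 can keep 108 per arm and 36 per clinic, and it states no power figure to amend. Recruiting 113 per group is not required. The cost is one reworded sentence and a slightly less favourable statement of the margin.

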**15. RANDOMISATION AND BLINDING**

In order to avoid sharing of messages among diabetic patients, different districts will be used for the control and the intervention. The guideline for the management of diabetes is similar across all the primary health centres in South Africa (Amod et al., 2012), thus, all the primary health care centres are eligible. Of all the eight municipalities/districts, two were conveniently selected. In each selected district, the diabetes clinics were assessed for available facilities such as human resources, HbA1c testing, available diabetes support programmes. The information were obtained from the various facilities or unit heads as deemed appropriate. The obtained information were scored and used to stratify the diabetes clinics into two levels; average and low resourced clinics. All the clinics were assigned an identification number which were hidden from the study statistician. One average-resourced and two low-resourced clinics were selected from the two selected districts, summing up to 6 clinics; 4 low resourced and 2 high resourced clinics. From the clinics selected, demographic and other basic information were obtained to screen for eligibility. From the sample size calculation, 108 participants are required in both arms of the study, therefore, 36 participants are required from each of the six selected clinics. After the collection of the baseline data, randomisation will take place, where individuals are randomly assigned to either the intervention or the control arm using a simple randomisation technique with a 1:1 allocation ratio using the assigned ID numbers. The study statistician will randomly select 36 participants from the list of eligible participants from each clinic, adjusting for age and mean duration of diabetes. Participants in the intervention arm will then be contacted to ascertain their preferences in terms of the preferred language of communication; either the locally spoken Xhosa language or English, preferred time of receiving SMSs, name and contact of next of kin or the available support person.

The treatment allocation will be concealed until the point of randomisation. However, due to the nature of the study, the selected districts for the intervention will be made aware of the intervention. Likewise, it will not be possible for research staff conducting the SMS intervention to be blinded to the intervention. However, the primary outcome, random fasting sugar will be blinded to treatment allocation since it is an objective measure.

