**12. STUDY SETTING AND POPULATION**

The study will be conducted at diabetes clinics in four randomly selected districts in the Eastern Cape Province, South Africa. The Eastern Cape Province was created in 1994, and include areas from the Xhosa homelands of the Transkei and Ciskei, as well as part of the Cape Province. The Eastern Cape Province is one of the poorest provinces in South Africa (Business Tech, 2016; StatsSA, 2011). The Eastern Cape Province is made up of two metropolitan municipalities; Buffalo City Metropolitan Municipality and the Nelson Mandela Bay Metropolitan Municipality and six district municipalities. The six district municipalities are; Alfred Nzo, Amathole, Chris Hani, Joe Gqabi, OR Tambo and Sarah Bartman districts municipalities (Wikipedia, 2017).

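### Section 15 gives two incompatible units of allocation, district and individual; under the district reading with two districts, the SMS effect cannot be separated from district

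*Protocol*

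**What the plan says.** Section 15 opens with a measure against message sharing: "different districts will be used for the control and the intervention". Later in the same section, after baseline data collection, "individuals are randomly assigned to either the intervention or the control arm using a simple randomisation technique with a 1:1 allocation ratio", using participants' ID numbers. The blinding paragraph returns to districts: "the selected districts for the intervention will be made aware of the intervention".

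The districts themselves are also described in two ways. Section 12 refers to "diabetes clinics in four randomly selected districts in the Eastern Cape Province". Section 15 says: "Of all the eight municipalities/districts, two were conveniently selected". On clinics, Section 15 says: "One average-resourced and two low-resourced clinics were selected from the two selected districts, summing up to 6 clinics", that is, three per district. It adds that "36 participants are required from each of the six selected clinics".

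Section 11 calls the study a randomised controlled trial. Section 14 computes power for independent participants, with no design effect. Section 21 names an intention-to-treat comparison of the two groups by linear regression and is silent on clinic and district.

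**The concern.** The unit of allocation determines what the trial can estimate. If each arm has its own district, participants are not individually randomised. If participants are individually randomised across the six clinics, each district contains both arms and the separation that opens Section 15 does not exist. The sentence about telling the intervention districts makes sense only if whole districts are intervention districts, so the opening sentence is hard to dismiss as a stray remnant.

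Either reading defeats something that the protocol relies on. Under district allocation, a difference between districts in staffing, case mix or routine care would appear as an SMS effect. The protocol describes no random assignment of districts to arms. Balancing age, diabetes duration and blood sugar at baseline (Section 16) would not remove such a difference. Under individual allocation, both arms attend the same clinics and nothing stated prevents message sharing. As written, staff cannot tell which procedure to follow.

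**Working it through.** **Inputs from the protocol.** Section 14: difference 0.5, SD 1, two-sided alpha 5%, 90 per arm, 108 per arm after allowing for 20% loss. Section 15: two districts, six clinics, 36 participants per clinic. Section 12: four districts. The protocol gives no intraclass correlation (ICC); 0.01 to 0.05 is an assumed range.

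**1. The plan's own power.** For independent participants the noncentrality is 0.5/√(2/90) = 3.354. With 178 df the noncentral t gives 91.6% (normal approximation 91.8%), which agrees with over 90%. With 108 × 0.8 = 86.4, taken as 86 per arm, the power is 90.3%. The figure is sound for individual randomisation.

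**2. Does the recruitment arithmetic settle the unit?** No. Three clinics × 36 = 108 per arm fits one district per arm. Six clinics × 36 = 216 = 2 × 108 fits either reading.

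**3. Degrees of freedom by district.** Two districts, one per arm: 2 − 2 = 0, so no valid district-level test or power exists. Four districts split two against two (an assumption): 4 − 2 = 2. Confounding is then not total, but the individual-level power still does not apply.

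**4. Type I error if clustering by district is ignored (illustration).** Design effect DE = 1 + (90 − 1) × ICC; true alpha = 2 × [1 − Φ(1.96/√DE)].

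| Assumed ICC | DE | True alpha |
|---|---|---|
| 0.01 | 1.89 | 15% |
| 0.02 | 2.78 | 24% |
| 0.05 | 5.45 | 40% |

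**5. A milder case: district ignored, clinics as clusters (illustration).** Three clinics per arm, 36 × 0.8 = 28.8, taken as 29 evaluable each, so 87 per arm. DE = 1 + 28 × ICC; effective n = 87/DE; noncentrality = 0.5/√(2 × DE/87); df = 6 − 2 = 4.

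| Assumed ICC | DE | Effective n per arm | Power, 4 df | True alpha if clustering is ignored |
|---|---|---|---|---|
| 0 | 1.00 | 87 | 70% | 5% |
| 0.01 | 1.28 | 68 | 60% | 8% |
| 0.02 | 1.56 | 56 | 52% | 12% |
| 0.05 | 2.40 | 36 | 37% | 21% |

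The fall from about 91% to 70% comes from having only 4 df; the rest comes from the assumed ICC.

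**6. Cost of message sharing under individual randomisation.** If a fraction c of controls receives the full effect, the difference becomes 0.5 × (1 − c). With 86 per arm (noncentral t): c = 10% gives 0.45 and power 84%; c = 20% gives 0.40 and 74%; c = 30% gives 0.35 and 63%. These fractions are assumptions.

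All the power figures carry over Section 14's 0.5 SD, which was set for HbA1c. The primary outcome in Section 17 is random blood glucose, for which the protocol gives no effect size or SD.

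**The case against.** The strongest reply is that only one sentence in Section 15 states an allocation mechanism, and it is individual: after baseline, by ID number, 1:1. The statement that allocation is concealed until randomisation fits it, and so do Sections 11 and 14. On that reading the power reproduces. This stands, and it is why the harm must be put conditionally. A reader might infer that the trial is already a confounded two-district comparison with invalid power. The documents do not support that; they support an unresolved contradiction, one side of which has that result.

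A reader might also infer that the regression in Section 21 is wrong because it names no clinic or district term. That does not follow. The section neither includes nor excludes such terms, and that detail may sit in a statistical analysis plan. The absence of between-district degrees of freedom with one district per arm does not depend on it.

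Total confounding also needs the two districts of Section 15. With Section 12's four it would be partial. The past tense of Section 15 favours two, though its plural reference to intervention districts sits more easily with four.

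Finally, the protocol had a reason for separating districts. Giving that up has a price, which step 6 shows is not negligible.

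**Conclusion.** The contradiction is certain and must be resolved before anyone is allocated: two units of allocation within Section 15, and two incompatible accounts of the number and selection of districts between Sections 12 and 15.

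The consequence is conditional. With one district per arm, no analysis can separate SMS from district, and the stated power does not apply. That conclusion needs no assumed ICC. The error rates of 15% to 40% (district as cluster) and 8% to 21% (clinic as cluster), and the clinic-level power of 60% to 37%, are illustrations. They rest on an assumed ICC of 0.01 to 0.05. The clinic-level power is not the power of the one-district-per-arm design, which has none. If participants are individually randomised, the power of over 90% stands on Section 14's own assumptions, but protection against message sharing is gone.

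**What to change.** State one unit of allocation and align Sections 12, 14, 15 and 21 with it. The option that fits Sections 11, 14 and 21 is individual 1:1 randomisation in all six clinics:

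- Delete the opening sentence of Section 15 that separates the arms by district, and the later sentence about informing the intervention districts.
- If randomisation is done within each clinic, say that it is stratified by clinic, since this changes the simple randomisation now stated.
- Give one number of districts and one selection method in Sections 12 and 15.
- At six months, ask controls whether they saw study messages. Report the answers descriptively as a measure of contamination and keep intention-to-treat as the primary analysis.

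This costs protocol wording and one questionnaire item, and no extra participants as long as sharing is small. The question measures sharing but does not prevent it, and the power losses in step 6 are the price if sharing is common.

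If district allocation is truly intended, the protocol must stop describing individual randomisation, withdraw the power of over 90%, and state that with one district per arm the effect is confounded with district. Randomising a larger number of clinics or districts as clusters is a legitimate alternative, but it needs a new sample size calculation.

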**9.3.1 Glycated haemoglobin (HbA1c)**

Glycated haemoglobin (HbA1c) is utilised to detect type-2 DM and pre-diabetes. It shows an individual’s average blood glucose level over the past three months without any daily changes. It is considered a convenient method, as it does not require fasting and it is time independent (American Heart Association, 2016; National Health System, 2016; NIDDKD, 2016). This tool has been validated and accepted as a diagnostic tool for diabetes. It was formerly used for monitoring blood glucose (WHO, 2011:6).

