**9.3.3 Fasting plasma glucose (FPG)**

Fasting plasma glucose (FPG) is another tool used in the diagnosis of diabetes and pre-diabetes. It a more convenient and cost-effective tool than the oral glucose tolerance test. It requires the individual to fast for eight hours prior to the test, which is conducted, preferably, in the morning (American Heart Association, 2016; National Health System, 2016; NIDDKD, 2016).

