**17. PRIMARY OUTCOME MEASURE**

**17.1 Glycaemic control**

The primary outcome measure is a change in glycaemic control from baseline to six months, measured as mean random blood glucose level. This will be assessed using a point-of care device which analyses a drop of fingertip capillary blood.

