**21. DATA ANALYSIS**

All treatment evaluations will be performed on the principle of intention-to treat (ITT), using the observed data collected from all randomised participants. Comparison of the baseline and the subsequent readings of the HbA1c will be determined. Primary outcome will be analysed with the chi-square. Descriptive statistics will be used to summarise the demographic and baseline characteristics. Continuous variables will be summarised as numbers of observed values, means, standard deviation, median, minimum and maximum. Categorical variables will be described as frequency and percentage. Linear regression model will be used to test the effect of intervention on the primary outcome between the two groups. All statistical tests will be two-sided at 5% significance level. The Statistical Package for Social Sciences (SPSS) version 22 will be used for all statistical analysis.

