**25. RESEARCH BUDGET**

| **Activity** | **Estimated Cost** |
| --- | --- |
| Printing of questionnaires for the baseline and final data collection | R10000 |
| Printing of informed consent | R8000 |
| Employment of Research Assistants for data collection at baseline and at 6 months | R40,000 |
| Procurement of instruments (Laptop, data storage device, Point of care device for sugar, test-stripes for sugar) Blood pressure apparatus, height and weight scale) | R30000 |
| Employment of Nurses involved in dispatching SMS and follow-up for the period of 6 months | R30,000 |
| Procurement of recharge cards for disseminating SMS for the period of study | R40000 |
| Data Capturing at baseline, 3 months and 6 months | R20,000 |
| Logistics(accommodation during data collection, transport, miscellaneous) | R22,000 |
| Data Analysis | R15,000 |
| Language Editing | R10000 |
| Printing and binding of dissertation | R7,000 |
| Presentation of results at Conferences | R15,000 |
| Printing and binding of dissertation | R3000 |
| Total | R250,000 |

26. **REFERENCES**

Adisa, R. & Fakeye, T.O. (2014). Treatment non-adherence among patients with poorly controlled type 2 diabetes in ambulatory care settings in southwestern Nigeria. *African Health Sciences*, 14(1):1–10.

Aikens, J.E. & Piette, J.D. (2012). Longitudinal association between medication adherence and glycaemic control in type 2 diabetes. *Diabetic Medicine*, 30: 338–345.

American Diabetes Association (2011). Standards of Medical Care in Diabetes-2011. *Diabetes Care*, 34(1):S11–S61.

American Diabetes Association (2015). *Definition of Diabetes. Definition of diagnosis*. Available at: http://www.diabetes.org/diabetes-basics/diagnosis/ [Accessed June 22, 2015].

American Diabetes Association (2003). Treatment of hypertension in adults with diabetes. *Diabetes Care*, 26(Supplement 1): 80–82.

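### Sections 14, 15, 17.1 and 21 do not describe one primary glycaemic variable, and Section 15 calls the outcome blinded without any masking procedure

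*Protocol*

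**What the plan says.** The Protocol describes the glycaemic endpoint in several places.

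- **Section 17.1** defines it: "The primary outcome measure is a change in glycaemic control from baseline to six months, measured as mean random blood glucose level". On the method it adds: "This will be assessed using a point-of care device which analyses a drop of fingertip capillary blood". It sets no time of day or meal condition, and does not say whether the mean is over several readings per person or over the group.
- **Section 15** gives another label and a blinding claim: "the primary outcome, random fasting sugar will be blinded to treatment allocation since it is an objective measure". The same section accepts that the intervention districts and the staff running the SMS programme will know the allocation.
- **Section 21** says: "Comparison of the baseline and the subsequent readings of the HbA1c will be determined". No other glycaemic variable is named there. The next sentence assigns a chi-square test to the primary outcome, and a later one assigns linear regression.
- **Section 14** bases the sample size on an extra HbA1c reduction of 0.5% with SD 1.
- **Section 16** lists random blood sugar as the only biochemical measurement at baseline. **Sections 17 and 18** list no HbA1c outcome. **Section 25** pays for a glucose meter and strips, and no HbA1c test is itemised.
- **Section 13.1** admits participants on HbA1c above 7.0% or on a random morning glucose above 10 mmol/L.
- **Section 10.2**, in the theoretical framework, mentions HbA1c among the things to be assessed after the intervention.

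**The concern.** The primary outcome is the one variable a protocol must fix without ambiguity. Here the label in the blinding section contradicts itself, the outcome section names glucose, and the analysis and sample size sections speak of HbA1c. Someone following the text would carry out an HbA1c comparison for which no collection is planned, and would report a power that belongs to a different variable from the one measured.

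The sampling condition matters too. Section 9.3.1 credits HbA1c with convenience, "as it does not require fasting and it is time independent", and describes it as an average over three months. A random glucose reading has neither property. Screening by glucose uses a morning reading, but the outcome reading has no such condition. The SMS content includes diet advice and reminders about glucose checks and medication, so behaviour around the visit could differ by arm unless sampling is standardised.

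Finally, objectivity describes the instrument, and blinding describes who knows the allocation. A fingertip reading taken by someone who knows the arm is unmasked, however objective the meter. Reported as written, the trial would claim a protection that no described procedure provides.

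**Working it through.** **1. Can the Section 15 label be met?** Of fasting glucose, Section 9.3.3 says: "It requires the individual to fast for eight hours prior to the test". A random sample carries no such condition, so no sample satisfies both words.

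**2. Which variable does each section use?**

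| Section | Variable |
| --- | --- |
| 13.1 Entry | HbA1c or random morning glucose |
| 14 Sample size | HbA1c |
| 15 Blinding | random and fasting sugar |
| 16 Baseline data | random blood sugar |
| 17.1 Primary outcome | change in mean random capillary glucose |
| 18 Secondary outcomes | neither |
| 21 Analysis | HbA1c |
| 25 Equipment | glucose meter and strips |

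What is collected and paid for is glucose. What is sized and named in the analysis is HbA1c. Because Section 13.1 accepts entry on glucose alone, a baseline HbA1c is not assured even from screening.

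**3. What does the stated power refer to?** Inputs from Section 14: difference 0.5, SD 1, two-sided 5%, 90 per arm. The normal approximation is power = Φ(difference/SD × √(n/2) − 1.960).

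- 90 per arm: 0.5 × √45 = 3.354; 3.354 − 1.960 = 1.394; power 0.918.
- 108 per arm less 20% loss: 108 × 0.8 = 86.4, so 86 per arm; 0.5 × √43 = 3.279; 3.279 − 1.960 = 1.319; power 0.906.

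The claim of over 90% therefore reproduces, for HbA1c.

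**4. Does it carry over to glucose?** Only if the true glucose difference is about half the SD of the analysed quantity, which is the standardised difference behind Section 14 (0.5/1). The Protocol gives neither figure in mmol/L. As an illustration only, assume a difference of 1.0 mmol/L and 90 per arm:

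| Assumed SD (mmol/L) | Power | n per arm for 90% |
| --- | --- | --- |
| 2 | 0.92 | 85 |
| 3 | 0.61 | 190 |
| 4 | 0.39 | 337 |
| 5 | 0.27 | 526 |

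The range shows that the power cannot be read across. It does not estimate the trial's actual power.

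**5. Is any masking described?** Objectivity is the only reason given, and nobody is named as a masked assessor. Section 25 has one line for "Employment of Research Assistants for data collection at baseline and at 6 months" and a separate line for nurses who send the SMS, so separate staff exist on paper, but no rule uses that separation. Section 15 says that different districts serve the two arms, and also that individuals are randomised 1:1. If the first holds, the clinic itself reveals the arm and withholding a list masks nobody.

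**The case against.** The strongest defence is that Section 17.1 is the defining section and is clear, that Sections 16 and 25 agree with it, and that one stray word in Section 15 is a drafting slip. That probably explains the word, so it would go too far to say that clinics will measure different quantities. It does not explain why Sections 14 and 21 rest on HbA1c.

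Three stronger readings are tempting and are not supported.

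- *Section 21 makes HbA1c the primary outcome.* It does not say so. The HbA1c sentence and the sentence on the primary outcome are separate. What stands is that no other glycaemic variable is named there.
- *The HbA1c comparison cannot be done.* Section 10.2 mentions HbA1c at the end of the intervention, Section 15 says clinics were assessed for HbA1c testing, and usual-care tests continue under Section 16. Some values may exist. What stands is that the data collection plan and budget do not provide for them, so source and completeness are unstated.
- *Uncontrolled meal timing costs a calculable share of precision.* One could add an assumed meal-and-time SD to an assumed between-person SD and quote a percentage. The Protocol gives neither, and that sum describes a single final reading. For a change from baseline, the stable between-person part cancels and within-visit noise enters twice, so the percentage would not apply.

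It is also fair to say that selective timing or repeat readings are only a possibility; nothing in the Protocol suggests they will occur. But blinding is a statement about procedure, and none is given.

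**Conclusion.** The point holds as a contradiction within the Protocol, and it should be corrected before outcome data are collected. The primary outcome carries a self-contradictory label in Section 15 and is random capillary glucose in Section 17.1, while the sample size and the only glycaemic comparison named in Section 21 concern HbA1c, which Sections 16 to 18 and 25 do not provide for. The stated power is arithmetically right (0.918 at 90 per arm, 0.906 at 86) but applies to HbA1c only; for glucose it is unknown. The claim of blinding is unsupported by anything described.

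No size can be put on possible bias from unmasked or unstandardised readings. The glucose powers above rest wholly on an assumed difference and assumed SDs. Whether masking is achievable depends on whether arms are allocated by district or by individual, which Section 15 leaves unresolved.

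**What to change.** Name one glycaemic variable and use it in Sections 14, 15, 17 and 21. Which one is the sponsor's choice.

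If the measure now collected and funded, random capillary glucose, is kept:

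1. Delete the word *fasting* from Section 15.
2. Replace the HbA1c sentence in Section 21 with the glucose comparison.
3. Restate Section 14 in mmol/L with a justified difference and SD, or say that the power of over 90% applies to HbA1c only.
4. Take the reading in the same morning window, in line with the morning reading at screening, at baseline and six months in both arms, and record the first reading.
5. Time since the last meal may be recorded for a sensitivity analysis. It should not be a covariate in the primary model: at six months it is measured after randomisation and the messages may affect it, so adjusting for it could bias the treatment effect.

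If HbA1c is chosen instead, Section 14 can stand, but Sections 15, 16, 17 and 25 must provide for measuring it at both visits.

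In either case, replace the blinding sentence with a rule that the budgeted research assistants, not the SMS nurses, obtain the six-month measurement without access to allocation. If arms are allocated by district, so that the clinic reveals the arm, state that outcome assessment is not blinded.

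For the glucose option the cost is Protocol wording, a reworked sample size statement, an optional form field and a slightly narrower visit window. The two staff groups are already separate budget lines. The HbA1c option would add testing costs that the budget does not itemise.
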